### 9.2.2 Assessment of Secondary Outcomes

- Proportion of patients with HIV-RNA <50 cp/ml at week 48 by FDA snapshot. The following assumptions will be done:
  - a. Success is considered as HIV-RNA < 50 cp/ml in the snapshot time window;
  - b. Failures will be defined as one of the following categories, i.e.:
    - i. HIV-RNA  $\geq$  50 cp/ml;
    - ii. Change of therapy
    - iii. Discontinuation of therapy due to lack of efficacy;
  - c. No virological data will be defined as one of the following categories, i.e.:
    - i. Discontinued due to adverse event or death;
    - ii. Discontinuation of therapy due to consent withdrawal or loss to follow-up or other reason;
    - iii. Patients that are on study but have missing data in snapshot time window;
  - d. Snapshot time window is 48 weeks after the baseline visit  $\pm$  3 weeks (i.e. window size is half of the duration of the time between study visits);
- Loss of future drug options will be assessed in patients failing treatment, i.e. patients who will have 2 consecutive HIV RNA measurements  $\geq$ 100 copies/ml. For these patients, genotype resistance testing will be performed at the SHCS center according to their usual practice. Plasma samples will be collected at each visit, processed and stored at  $-80^{\circ}\text{C}$  at local virology laboratories. The same processing and storage conditions will be used as for SHCS samples. Genotype resistance interpretation will be centrally repeated by the Laboratory of Virology at HUG at the end of the study.
- CD4 cell count change: measurement of the CD4/CD8 fraction at local immunology or virology laboratories.
- HIV-DNA level change: HIV-DNA level will be measured in batch by a digital droplet PCR (ddPCR) assay using the RAINDANCE system. PBMC samples will be stored at randomization and at week 48 visit and the assay will be performed retrospectively in the Division of Infectious Diseases and Hospital Epidemiology, University hospital Zurich
- Lipidic profile changes: measurement of total cholesterol, LDL-cholesterol, HDL-cholesterol and triglycerides at local chemistry laboratories.
- Glucose level changes: measurement of glucose at local laboratories.

- Framingham-calculated cardiovascular risk changes: calculation using the Framingham 10 year CHD risk calculator by MDCalc: <http://www.mdcalc.com>. A printout of the result should be filed with the source documents.
- Glomerular function rate changes: measurement of plasma creatinine at the sites' local chemistry laboratories and calculation according to the CKD-EPI (Chronic Kidney Disease Epidemiology Collaboration) equation using the following online calculator: <http://www.qxmd.com/calculate-online/nephrology/ckd-epi-egfr>. A printout of the result should be filed with the source documents.
- Occurrence of adverse events: documentation in the electronic CRF by the study nurse or other (e.g. study coordinator, research associate).
- Occurrence of serious adverse events (SAE): documentation in the electronic CRF by the study nurse or other (e.g. study coordinator, research associate).
- Occurrence of CNS adverse events: documentation in the electronic CRF (log AE) by the study nurse or other (e.g. study coordinator, research associate).
- Presence of CNS symptoms: documentation in the electronic CRF (week 2 and 6 CNS questionnaire) by the study nurse or other (e.g. study coordinator, research associate).
- Weight changes: documentation in the electronic CRF by the study nurse or other (e.g. study coordinator, research associate).
- Health-related quality of life: assessment using the PROQOL-HIV instrument (87, 88) and a visual analog scale. These assessments will be performed at baseline, week 12 and week 48 by the study nurse/physician. The PROQOL-HIV questionnaire can be filled-in directly by the patient. Documentation on paper source document and transfer into the electronic CFR by the study nurse or other (e.g. study coordinator, research associate).
- Patient's monitoring satisfaction. Assessment using:
  - o Monitoring choice, for patients randomized in the patient-centered monitoring arm);
  - o Visual analogue scale (for all patients regardless of the randomization arm),
  - o Proportions of patients in the patient-centered monitoring arm expressing the willingness to change of monitoring option
- Patient's treatment satisfaction: assessing using visual analogues scale, patient's preferences about treatment, ARV regimen chosen for the post-study period and reason for change in case of change.
- Study satisfaction: assessment using 7 questions discussed at week 48.

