### 5.2 Secondary Outcomes

1. Proportion of patients maintaining HIV suppression defined as HIV-RNA <50 copies/ml throughout 48 weeks (+/- 21 days). A single blip defined as HIV-RNA <200 copies/ml during the study period is allowed as long as this value is followed by HIV-RNA <50 copies/ml;
2. Proportion of patients with HIV-RNA < 50 cp/ml at week 48 by FDA snapshot analysis; Proportion of patients experiencing loss of future drug options defined as new intermediate or high-level resistance to one or more drugs to which the patient's virus was considered sensitive at trial entry;
3. Time to loss of virological response (TLOVR) up to week 48 defined as the first of the two-confirmed HIV-RNA >100 copies/ml (at least two weeks apart);
4. Change in CD4 cell count from baseline to week 48 +/- 21 days;
5. Change in HIV-DNA level from baseline to week 48 +/- 21 days;
6. Change in lipidic profile (total cholesterol, high density lipoprotein-cholesterol, triglycerides, and low density lipoprotein-cholesterol) from baseline to week 48 +/- 21 days;
7. Change in glucose profile from baseline to week 48;
8. Change in Framingham-calculated cardiovascular risk from baseline to week 48;
9. Change in glomerular function rate from baseline to week 48;
10. Proportion of patients with an adverse event throughout week 48;
11. Proportion of patients with a serious adverse event (SAE) throughout week 48;
12. Proportion of patients with a CNS adverse event throughout week 48;
13. Proportion of patients new to DTG with CNS symptoms at 2 and 6 weeks after starting DTG;
14. Change in patients' health-related quality of life from baseline to weeks 12 and 48;
15. Assessment of patient's monitoring satisfaction from baseline to weeks 24 and 48 for patients in the patient-centered monitoring arm;
16. Assessment of the global satisfaction of the monitoring at week 48 for all patients (regardless of the randomisation arm);
17. Proportion of patients in the patient-centered monitoring arm expressing willingness to change monitoring options throughout 48 weeks;
18. Assessment of patient's treatment satisfaction at week 48;
19. Assessment of ARV treatment in the post study;
20. Study satisfaction at week 48;
21. Cost-effectiveness of study arms at 48 weeks;
22. Changes in patient weight from baseline to week 48.

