### 8.1.2 Control Intervention (standard/routine/comparator treatment)

Patients in the control intervention will be on fully suppressive antiretroviral regimen.

The control intervention may include several options:

- 2 NRTIs + either 1 NNRTI, 1 boosted PI or 1 INSTI;
- NRTI-sparing triple ARV regimen (e.g. 1 NRTI + 1 NNRTI + 1 INSTI);
- Dual therapy with protease inhibitor (such as PI + NRTI or NNRTI or INSTI).

Within-class antiretroviral switch (such as switch from TDF to TAF) are accepted during the study period only for patients randomized in the continuing cART arm. Other antiretroviral switch are discouraged and sponsor agreement is needed before the switch.

The following regimens will be excluded:

- Two-drug combinations with: 1 NRTI + 1 NNRTI, 1 NRTI + 1 PI without RTV, 1 NRTI + RAL, 2 NRTIs, MVC + RAL (not recommended by European guidelines);
- Triple NRTIs combination (not recommended by European guidelines);
- Dual therapy with DTG other than PI-based dual regimen, such as DTG + NRTI, DTG + NNRTI (simplified regimen already);
- PI monotherapy (simplified regimen already).

Standard monitoring includes a standard 12-weekly routine immunological and safety blood monitoring, including CD4 cell count, lipids and glucose, creatine kinase, renal and hepatic function tests, at affiliated SHCS sites.

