#### 11.4.2 Primary analysis

As a first step in this factorial trial, we will test for an interaction between the type of drug treatment and the monitoring type in order to assess if treatment effect is different depending on the type of monitoring. If the test is non-significant we will combine the two types of monitoring for the drug therapy comparison and the two drug therapies for the monitoring comparison. Otherwise, the trial will be analysed as a four-arm trial with a hierarchical testing approach.

For the primary comparison of the primary outcome between the two treatment arms, we will obtain the proportion of patients with viral suppression for 48 weeks in each arm, and compute a Mantel-Haenszel risk difference (DTG+FTC - cART) stratified for the monitoring type with a two-sided 95% confidence interval (107). If the lower confidence limit is higher than -12% we will conclude non-inferiority. If the lower confidence limit is below -12% we will conclude that DTG + FTC is potentially inferior to cART.

For the secondary comparison of the primary outcome between the two monitoring arms, we will calculate a Mantel-Haenszel test statistics and Mantel-Haenszel risk difference (DTG+FTC - cART) stratified for the type of treatment.

Secondary categorical outcomes (proportions of virological suppression <50 copies/mL both as a standard proportion and as FDA snapshot, of loss of future treatment options, of adverse events, of serious adverse events, of CSN adverse events, of CNS symptoms) between the DTG+FTC and cART groups, and between the patient-centered and standard monitoring groups will also be analysed using the Mantel-Haenszel test statistics and Mantel-Haenszel risk difference (DTG+FTC - cART) stratified for the type of monitoring and type of treatment, respectively.

For continuous outcome variables (CD4 count, HIV-DNA level, total cholesterol, high-density lipoproteine, triglycérides, low density lipoprotein-cholesterol, glucose, Framingham-calculated cardiovascular risk, glomerular function rate, weight, health-related quality of life, treatment satisfaction), we will compare the mean values at 48 months between the DTG+FTC and cART treatment groups and between the patient-centered and standard monitoring groups using linear regression adjusted for the type of monitoring and type of treatment, respectively.

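### The secondary FDA-snapshot rule scores any change of therapy as failure, although the protocol accepts within-class switches in the cART arm, and only there

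*Protocol*

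**What the plan says.** Section 5.2 names as secondary outcome 2 the "Proportion of patients with HIV-RNA < 50 cp/ml at week 48 by FDA snapshot analysis". Section 9.2.2 gives the algorithm:

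- Rule a: "Success is considered as HIV-RNA < 50 cp/ml in the snapshot time window".
- Rule b: "Failures will be defined as one of the following categories". The list is HIV-RNA at or above 50 cp/ml (i), "ii. Change of therapy", and discontinuation for lack of efficacy (iii).
- Rule c: no virological data, which covers discontinuation for adverse event, death, withdrawal, loss to follow-up or other reason, and missing data in the window.

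Section 8.1.2, on the control treatment, says that within-class switches "are accepted during the study period only for patients randomized in the continuing cART arm". It adds: "Other antiretroviral switch are discouraged and sponsor agreement is needed before the switch".

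Section 11.4.2 analyses the snapshot proportion with Mantel-Haenszel methods as a risk difference, DTG+FTC minus cART. The -12% decision rule in that section is written for the primary outcome. Section 5.1 defines that outcome by HIV-RNA below 100 copies/ml throughout 48 weeks, with no change-of-therapy component.

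**The concern.** Category b.ii cannot easily be read as efficacy-driven change only. Viraemia has its own line (b.i), so does lack of efficacy (b.iii), and discontinuations for safety or other reasons fall under c. What is left for b.ii is a change of regimen for any reason. That takes in the switch that 8.1.2 accepts as part of continuing cART.

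The patient at issue is suppressed, compliant with the protocol, and still on the control strategy as the protocol defines it. Scoring that patient as a failure lowers the control success rate for a reason unrelated to virological control. No corresponding accepted switch exists for DTG+FTC.

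The algorithm is also undecided, because such a patient meets rule a and rule b.ii at once. The trial is open-label, and section 11.3 says HIV-RNA results reach investigators within a week. The choice should therefore not be left until the data are seen.

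**Working it through.** **The plan's own figure.** The protocol states no size or power for the snapshot. Its non-inferiority calculation (section 11.2) is for the primary outcome: 97% versus 94%, margin 12 points, one-sided 0.025, power 80%.

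n = (1.960 + 0.842)² × (0.97×0.03 + 0.94×0.06) / (0.12 - 0.03)² = 7.849 × 0.0855 / 0.0081 = 82.8, so 83 per group. This reproduces the protocol. Then 166/0.9 = 184.4, consistent with the planned 184, or 92 per treatment group.

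**Inputs for the check.** p_C is true control success, 0.97 (section 11.2) or 0.92 (synopsis, statistical considerations). p_T is DTG+FTC success. s is the share of cART patients with a permitted within-class switch, an assumption because the protocol gives no rate. Switching is taken as unrelated to suppression, and stratification by monitoring type is ignored. The planning rates are for the primary outcome and are borrowed here.

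**Shift in the estimate.** Snapshot control success is p_C(1 - s), so the difference is p_T - p_C(1 - s) and the shift is p_C × s:

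| s | shift, p_C = 0.92 | shift, p_C = 0.97 |
|---|---|---|
| 1% | +0.92 points | +0.97 points |
| 5% | +4.6 | +4.85 |
| 10% | +9.2 | +9.7 |

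With 94% versus 97%, the difference moves from -3.0 to +1.85 points at s = 5% and to +6.7 at s = 10%. In counts, one reclassified patient among 92 moves the observed control rate by 1/92 = 1.09 points.

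**Therapy changes in the other arm.** Section 7.4 lists reasons to stop DTG+FTC and move to standard cART, including pregnancy, prohibited co-medication and serious adverse events. Section 8.6 adds changes to a DTG-free regimen. If a share l of otherwise successful DTG+FTC patients also fails the snapshot this way, the net shift is p_C × s - p_T × l. At s = l = 5%, with 97% and 94%, that is 4.85 - 4.70 = +0.15 points. If l exceeds s by enough, the net shift is negative.

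**Illustration against -12%.** This borrows a rule that the protocol does not state for the snapshot. Take true rates of 97% and 85%, a deficit equal to the margin, with 92 per group. Exact binomial enumeration with a Wald 95% interval gives these probabilities that the lower limit exceeds -12%:

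| s | l = 0 | l = 2% | l = 3% | l = 5% |
|---|---|---|---|---|
| 0 | 3.9% | – | – | – |
| 5% | 19.5% | 10.8% | 7.8% | 3.9% |
| 10% | 49.0% | 35% | 29% | 18% |
| 15% | 76.9% | – | – | – |

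For scale on l, section 3.2 cites adverse-event discontinuation of DTG of 2% to 3% in phase III trials and up to 13.7% in one cohort.

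**The case against.** A reader might infer that the rule biases the trial towards declaring non-inferiority. The documents do not support that. The hypothesis (11.1), the sample size (11.2) and the -12% rule (11.4.2) all concern the primary outcome, which ignores changes of therapy. The snapshot gets a test and a risk difference with no non-inferiority decision, and the protocol does not call it a key analysis. Secondary outcome 1 also reports suppression below 50 copies/ml without a change-of-therapy rule. This part of the objection stands in full.

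A reader might also infer that change-of-therapy failures arise in one arm only. They do not: b.ii applies to both arms, and DTG+FTC patients can lose snapshot success under sections 7.4 and 8.6. The direction of the net shift is therefore conditional, and the first column of the probability table rests on a one-sided assumption. This stands too. It does not cancel the misclassification, however. Those DTG+FTC patients have left their assigned treatment, whereas a permitted cART switcher has not.

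Third, rule a could be said to win for a suppressed switcher, or the term change of therapy could be said not to cover an accepted switch. The text says neither. It gives no precedence and no definition, so this reading shows the ambiguity without resolving it.

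Last, section 11.4.6 leaves analysis detail to a statistical analysis plan, which is not at hand and may settle the matter. But the protocol does not leave this rule open. It states the failure category and the permitted switch, and the two conflict as written.

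**Conclusion.** The conflict is real and confined to a secondary outcome. Followed literally, 9.2.2 b.ii scores suppressed, protocol-compliant cART patients as snapshot failures, and each 1% of such patients raises the DTG+FTC minus cART difference by about 0.92 to 0.97 points. That figure needs only the planning success rates and switching unrelated to suppression. How far the observed difference moves depends on the unstated switch rate and on regimen changes in the DTG+FTC arm. The probabilities of clearing -12% are illustrative only. The primary conclusion is not at risk. Severity is minor to moderate.

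**What to change.** Amend 9.2.2 b.ii to read: *Change of therapy, except a within-class switch accepted under 8.1.2; such patients are classified by their HIV-RNA in the week-48 window.* This also settles the overlap with rule a for these patients. Tabulate permitted switches and all other therapy changes by arm, and report the scoring that counts every change as failure as a sensitivity analysis.

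The cost is one sentence, one table and one extra run. Drug distribution and concomitant medications are already recorded at the study visits, and no treatment rule changes. It should be settled before the outcome data are analysed.

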DTG is well tolerated with only 2% to 3% of patients discontinuing the drug for adverse events in phase III trials. Frequent side-effects include sleep disturbance, gastro-intestinal complaints, headache, and respiratory tract complaints; most were grades 1 or 2 in clinical trials (13, 14). No life threatening adverse events were observed. Rates of psychiatric adverse events, i.e. insomnia, anxiety, depression or suicidality, were low in treatment-naïve phase III/IIb trials of DTG with frequency of withdrawal as low as 5% (51). However, observational studies have reported higher rates of central nervous system side effects (up to 20%) in treatment-naïve or -experienced patients receiving DTG (52, 53) with discontinuation rates due to central nervous system adverse events from 0.6% to 3.4% (52, 54-56). A retrospective cohort study in the Netherlands reported up to 13.7% of discontinuation rate due to adverse event on DTG (57) and another in Germany found that women and older patients were more at risk of discontinuing DTG for neuropsychiatric side effects (58). DTG is also lipid neutral with fewer elevations of low-density lipoprotein of grade 2 or higher compared to efavirenz or boosted darunavir in the SINGLE and FLAMINGO trials (12, 59). However, there are no data on the effect of DTG on body fat composition and the associated cardiovascular risk or bone mass density, which are growing concerns in our aging HIV population.

Drug interactions are very few (43), another advantage of the compound. DTG is a substrate of UGT1A1, CYP3A4, UGT1A3, and UGT1A9. Only 1% of potential drug-drug interactions are considered to be at risk (Figure 2). DTG should be used at the dose of 50mg twice daily with rifampicin, a potent inducer of UGT1A1 and CYP3A4. Co-administration with other inducers of UGT1A1 and CYP3A4 such as carbamazepin, oxcarbamazepin, phenytoin, phenobarbital and St. John's wort should be avoided. As DTG inhibits the renal transporter OCT2, it is contraindicated with the antiarrhythmic dofetilide (which is not authorized in Switzerland) and caution is needed when co-administered with metformin. DTG should be taken with food when administered with calcium or iron supplementation or vitamins intake as well as with magnesium or aluminium-containing antacids (14).

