### **4.4 Safety Objectives**

The study aims to assess the safety of DTG + FTC dual therapy and simplified ART monitoring throughout 48 weeks by evaluating the following parameters:

- Loss of future drug options in case of virological failure defined as new intermediate or high-level resistance to one or more drugs to which the patient's virus was considered sensitive at trial entry;
- Change in CD4 cell count, total cholesterol, low density lipoprotein-cholesterol, Framingham-calculated cardiovascular risk, and glomerular function rate;
- Occurrence of adverse events;
- Occurrence of serious adverse events;
- Occurrence of CNS adverse events in patients new to DTG.

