# **9. STUDY ASSESSMENTS**

## 9.1 Study flow chart(s) / table of study procedures and assessments

|                                                                    | Screening              | Year 1         |                |                |                |                |                |
|--------------------------------------------------------------------|------------------------|----------------|----------------|----------------|----------------|----------------|----------------|
|                                                                    | -4 weeks to
-1 week | Day 0          | Week 6         | Week 12        | Week 24        | Week 36        | Week 48        |
| Eligibility screen                                     | X                      | X              |                |                |                |                |                |
| Written informed consent                                           | X                      |                |                |                |                |                |                |
| Demographics                                                       | X                      |                |                |                |                |                |                |
| HIV-related data and medical history                   |                        | X              |                |                |                |                |                |
| Concomitant medications                                |                        | X              | X              | X              | X              | X              | X              |
| Full physical examination by physician                 |                        | X              |                |                | X              |                | X              |
| Allocation (double randomization)                                  |                        | X              |                |                |                |                |                |
| Start DTG + FTC OR remain on standard cART                         |                        | X              |                |                |                |                |                |
| Start patient-centered monitoring OR remain on standard monitoring |                        | X              |                |                |                |                |                |

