#### *Laboratory assessments:*

- HIV-1 RNA in plasma. If the baseline visit is performed within 7 days from the HIV-RNA measurement used for the screening visit, it is not mandatory to repeat the HIV-RNA measurement at the baseline visit. In such cases, HIV-RNA result used for the screening visit will be entered as well for the baseline visit in the database.
- Sample plasma and cells sample storage. If a venipuncture is planned at the baseline visit only for storages and the patient is included into the SHCS, plasma and cell sample storage can be drawn at the screening visit.
- HIV-1 DNA from PBMCs by ddPCR (performed retrospectively)
- DTG-related pharmacogenetics host profile will be performed for all patients on DTG. This analysis will be performed retrospectively according to funding availability and only for patients included in the SHCS and who have signed a consent form for genetic studies.

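### The renal outcome is creatinine-based eGFR, so starting dolutegravir may produce an apparent fall in the DTG + FTC arm without any change in filtration

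*Protocol*

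**What the plan says.** Renal function appears three times in the protocol as an outcome or objective. Section 4.4 lists change in "Framingham-calculated cardiovascular risk, and glomerular function rate" among the safety parameters. Section 5.2, item 9, has "Change in glomerular function rate from baseline to week 48" as a secondary outcome, and section 5.4, item 5, repeats it as a safety outcome.

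Section 9.2.2 fixes the measurement: "measurement of plasma creatinine at the sites' local chemistry laboratories and calculation according to the CKD-EPI" equation. In the flow chart (section 9.1) and in section 9.2.4.2, creatinine is the only renal test in the safety chemistry.

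The randomised contrast on day 0 is "Start DTG + FTC OR remain on standard cART". For continuous outcomes, including this one, section 11.4.2 states "we will compare the mean values at 48 months between the DTG+FTC and cART treatment groups", by linear regression adjusted for the monitoring arm. No baseline term is mentioned. I read the 48 months as week 48, since follow-up in the main trial is 48 weeks.

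Section 3.2 says "As DTG inhibits the renal transporter OCT2, it is contraindicated with the antiarrhythmic dofetilide" and asks for caution with metformin. It draws no consequence for creatinine.

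**The concern.** Creatinine leaves the blood partly by filtration and partly by tubular secretion. A drug that blocks a renal transporter can reduce the secreted part, so serum creatinine rises and any creatinine-based eGFR falls while filtration stays the same. The protocol names such a transporter effect for DTG and then uses creatinine as its only measure of filtration in a comparison where one arm starts DTG. Randomisation does not remove this, because the assignment itself causes it. It is a measurement bias in the marker.

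Two readings could go wrong. An apparent fall on DTG + FTC could be reported as renal harm. Or a real gain could be hidden: section 3.1 gives less tenofovir-related renal toxicity as a reason to simplify, and the artefact works in the opposite direction.

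**Working it through.** The protocol gives no expected eGFR change and no SD, so there is no figure of its own to reproduce. What follows is an illustration.

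**From the protocol.** 92 patients per treatment arm (synopsis and section 11.2). Creatinine at screening and week 48 for everyone, and at weeks 12, 24 and 36 in the standard-monitoring arm only (sections 9.1 and 9.3). At week 6, patients new to DTG have CK and liver tests, but creatinine only if they also take metformin. INSTI-containing regimens are allowed at entry and in the control arm (sections 7.1 and 8.1.2), so some patients in both arms may already take DTG. Their share is not given.

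**Assumed.** Baseline eGFR 90 ml/min. Creatinine rise c of 5% to 15% on starting DTG. Share s of the DTG + FTC arm new to DTG, 40% to 100%. No cART patient starts DTG. CKD-EPI exponent −1.209, which applies above the equation's creatinine breakpoint; below it the exponent is shallower (−0.411 in men, −0.329 in women) and the fall would be smaller.

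**Artefactual arm difference** = 90 × (1 − (1 + c)^−1.209) × s:

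| c | s = 40% | s = 70% | s = 100% |
|---|---|---|---|
| 5% | 2.1 | 3.6 | 5.2 |
| 10% | 3.9 | 6.9 | 9.8 |
| 15% | 5.6 | 9.8 | 14.0 |

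**Standard error** = SD × √(2/92):

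- SD of change 10: 1.47
- SD of change 15: 2.21
- SD 20, assumed for week-48 levels, which is what section 11.4.2 compares: 2.95

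**z = difference / SE**, from unrounded values:

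| Case | SD 10 | SD 15 | SD 20 |
|---|---|---|---|
| Low (2.1) | 1.4 | 0.9 | 0.7 |
| Middle (6.9) | 4.7 | 3.1 | 2.3 |
| High (14.0) | 9.5 | 6.3 | 4.7 |

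The low case is below 1.96 at every SD. The middle and high cases are above it.

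**Cross-check with other assumptions.** Take a fall of 8 ml/min in patients new to DTG, SD 15 and 92 per arm. The chance of p < 0.05 from the artefact alone is about 95% if nobody already takes DTG. It is about 82% if 20% in both arms do (mean difference 8 × 0.8 = 6.4) and about 58% if 40% do (8 × 0.6 = 4.8). Over falls of 4 to 12, SDs of 12 to 18 and prior DTG shares of 0 to 40%, the chance runs from 15% to nearly 100%.

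**The case against.** The strongest objection is that the decisive link is not in the document. Section 3.2 draws consequences from OCT2 inhibition for dofetilide and metformin only. Nothing in the protocol says that DTG raises creatinine, by how much, or as a fixed step. This stands, and it is why the point is conditional and its size assumed.

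A second objection is that significance is not assured. This also stands: the low case is not significant, and a comparison of week-48 levels is noisier than one of changes. A reader might infer that the planned regression would probably report a significant loss of kidney function. The documents do not support that, because neither the share new to DTG nor any SD is given.

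Third, the contrast may be weaker than modelled. Section 8.1.2 accepts within-class switches in the cART arm, so some control patients on another INSTI could move to DTG during the trial. That would dilute the artefact without removing it.

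Fourth, section 9.2.2 already discloses that the value comes from creatinine, and subgroup tables usually belong in the statistical analysis plan, which section 11.4.6 promises. This carries part of the way. However, the marker and its label as glomerular function are fixed in the protocol itself. The mixed models in section 11.4.3 could show the timing of a change only in the standard-monitoring half, where creatinine is repeated, and they do not separate patients by prior DTG use.

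**Conclusion.** The point holds in conditional form. The plan uses creatinine-based eGFR as its only measure of filtration, compares it between an arm that starts DTG and one that continues cART, and makes no allowance for the transporter effect that the protocol itself describes. An apparent eGFR fall may therefore appear among patients who start DTG with no change in filtration, and it may mask a benefit of dropping tenofovir.

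The illustrated arm difference is about 2 to 14 ml/min. It rests entirely on the assumed creatinine rise, share new to DTG, baseline eGFR and CKD-EPI exponent.

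A reader might go further and say that the renal safety question is left unanswered. That is too strong, since creatinine-based eGFR can still show a large decline. Severity is low: this is one secondary and safety outcome, it has no hypothesis in section 11.1, and it enters neither the non-inferiority decision nor the cost comparison.

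**What to change.** 1. Name the outcome *change in creatinine-based eGFR* in sections 4.4, 5.2, 5.4 and 9.2.2.
2. Analyse change from baseline with baseline adjustment, in place of week-48 means alone.
3. Report the arm contrast separately by whether the entry regimen contained DTG, defined the same way in both arms. Because this is a pre-randomisation characteristic, the comparison within each stratum remains a comparison of randomised groups.
4. State in advance that a difference seen only in patients new to DTG is not evidence of reduced filtration.
5. Show the week-12 to week-48 change in the standard-monitoring half as supportive only. It uses about 184/4 = 46 patients per arm and misses any true change, harm or recovery, before week 12.

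The cost is a wording change and one table from data already collected. Precision within strata will be lower, and the stratum already on DTG may be small, so it should not carry the whole conclusion. Cystatin C on the plasma stored at baseline and week 48 is an optional addition. It is an extra assay, and whether consent covers it cannot be seen from the protocol.
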